### Outcomes

#### Feasibility evaluation

The evaluation of feasibility will investigate the time economy and expressiveness of the measurement methods used in terms of quality and quantifiability. In this context, it will also be determined whether all the measurements are required for further investigations. Therefore, the results of the ultrasound techniques will be compared with the already more established methods to analyse their dependability and accuracy. Shear motion analysis will be compared with the more established flexibility tests and the analysis of compressibility with the mechanical tissue deformation resistance (indentometry). Furthermore, the ultrasound measurements will be assessed by the investigator in terms of their qualitative presentability and their related analysis procedures regarding to their manageability by using a five-level Likert-type scale (from very good to very bad) after each measurement. All measurement methods will be evaluated for their time economy by measuring the time needed for each measurement process. Also, the measuring instruments used will be critically ranked by the therapist and the investigator using a five-level Likert-type scale (from strongly agree to strongly disagree). The ranking will be based on the recorded outcomes to evaluate whether they are suitable to assess short-term and long-term changes in the selected treatments and at the chosen measurement time points. Afterwards, both experts will be asked for suggestions to optimise and adapt the study protocol.

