### Statistical analysis

Statistical analysis will be performed with SPSS Statistics 25 (IBM). Usual descriptive statistics will be used to summarise the results. Means per group, mean differences between the groups will be outlined with standard deviation, 95% confidence interval, minimum, and maximum. Baseline sample characteristics of the groups will be compared by using a single factor analysis of variance or in case of missing assumptions with the Kruskal-Wallis test. Qualitative variables like experiences in myofascial self-treatments and “preferred free leg” will be analysed by using a chi-squared test. Main outcomes like shear motion (distance in mm) and flexibility (range of motion in degree) will be analysed for the three measurement time points in the short-term evaluation as well as for all measurement time points of the IAMT group and the control group in the long-term evaluation by using a longitudinal generalised linear mixed model. Those analyses will include groups, time (measurement time points), and group by time interaction as fixed effects, each participant as random effect, and a covariance structure that provided the best fit for the model to obtain estimates of slopes before and after the treatment and compared between groups like age, experiences in myofascial self-treatments, and “preferred free leg”. The Kruskal-Wallis test will be used to compare the experts ranking of suitability of the measuring instruments, whereas the time economy of the measurement instruments used will be analysed by using a single factor analysis of variance, if the necessary assumptions will be met. To evaluate the quantitative expressiveness of the ultrasound measurements with those of the flexibility tests and the indentometry, their relationship will be analysed by Pearson’s correlation coefficient, if the outcomes will be distributed normally, otherwise Spearman’s correlation coefficient will be applied. The significance level for all tests will be 5%.

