In this pilot investigation, modern and objective testing methods will be applied first to healthy female soccer players to evaluate the feasibility of the planned measurement protocol and treatment timeframes in the context of IAMT and, if necessary, to adapt them. Furthermore, the information generated about the effects of IAMT should build first references for the sample size calculation of further full studies. If this study protocol proves feasible to implement, the next step will be a full study. Then, studies of male soccer players and of athletes from other sports would follow. In addition, the effects of IAMT on both athletes and non-athletes with low back pain and its potential impact on strength development in healthy athletes, present an exciting spectrum of future full studies.

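### Both tests planned for the feasibility primary outcome assume independent observations, but the ratings come from the same two experts and the timings from the same players.

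*Protocol article*

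**What the plan says.** The Aims section of the protocol article puts the time economy and expressiveness of the measurement methods first among the primary outcomes.

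- **Who rates.** In the Feasibility evaluation section, "the measuring instruments used will be critically ranked by the therapist and the investigator using a five-level Likert-type scale". The same section ends with "both experts will be asked for suggestions to optimise and adapt the study protocol", which confirms that there are two raters.
- **What is rated.** The question is "whether they are suitable to assess short-term and long-term changes in the selected treatments and at the chosen measurement time points". The number of items per instrument is not given.
- **What is timed.** That section also has the time recorded for each measurement process, for all methods. Under Study design, players are measured before, immediately after and 45 min after treatment. The IAMT and placebo groups are measured again in weeks three and five.
- **How it is analysed.** In the Statistical analysis section, "The Kruskal-Wallis test will be used to compare the experts ranking of suitability of the measuring instruments", and the "time economy of the measurement instruments used will be analysed by using a single factor analysis of variance", on condition that its assumptions are met. All tests use a 5% level. A participant random effect is specified in the same section, but only for the main outcomes such as shear motion and flexibility.

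**The concern.** Kruskal-Wallis and a single-factor ANOVA both need independent observations in each group. Here the groups are the instruments or methods, and the same people supply the data for every group: two experts for the ratings and the same players for the timings. Neither test fits the data that the Feasibility evaluation section describes.

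With two raters there is a second problem. The rating test can hardly reach 5% whatever the experts think, so a non-significant result would say little about whether the instruments differ. For the timings, the nominal 5% is not the real error rate. Both results feed the judgement on which measurements a full study should keep.

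**Working it through.** The article gives no power or precision figure for either analysis, so there is nothing to reproduce.

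**Ratings: inputs.** Two raters (stated). One rating per rater per instrument (assumed). The number of instruments *k* is not stated. The article describes four main devices (ultrasound, inclinometer, indentometer, thermometer), or five with the skinfold calliper. The measurement order lists six measures. Splitting flexibility into its three tests gives 6 − 1 + 3 = 8.

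**Ratings: smallest attainable p.** With tie correction, H = (N − 1) × SSB/SST on the ranks, where N = 2k. The maximum occurs when both experts agree on every instrument. Then SSB = SST and H = 2k − 1, referred to chi-square with k − 1 degrees of freedom.

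| k | largest H | smallest asymptotic p |
|---|---|---|
| 3 | 5 | 0.082 |
| 4 | 7 | 0.072 |
| 5 | 9 | 0.061 |
| 6 | 11 | 0.051 |
| 7 | 13 | 0.043 |
| 8 | 15 | 0.036 |

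The Friedman test, which does respect the pairing by rater, does not help. Its largest value with two raters is 2(k − 1), so its smallest asymptotic p is 0.112 at k = 4 and 0.075 at k = 6.

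**Timings: inputs.** 60 players (the stated minimum), three short-term sessions (stated), four methods (assumed). Variance shares are assumed: P for player, M for player-by-method, E for residual, with P + M + E = 1.

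**Timings: direction of the error.** Suppose each of t sessions enters as a separate row. Differences between method means then depend on a variance of (M + E/t)/n, because the player effect cancels. The one-way ANOVA uses about (P + M + E)/(nt) instead. The ratio of true to assumed variance is

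R = (tM + E)/(P + M + E).

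R below 1 makes the test conservative and R above 1 makes it anti-conservative. As a large-sample approximation, the type I error is P(chi-square with 3 df > 7.85/R), where 7.85 is 3 times the 5% critical F. The last column is from 4,000 simulated null trials per setting, t = 3.

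| P / M / E | R | approximate type I error | simulated |
|---|---|---|---|
| 0 / 0 / 1 | 1.0 | 5% | 5.0% |
| 0.3 / 0 / 0.7 | 0.7 | 1.1% | 1.1% |
| 0.5 / 0 / 0.5 | 0.5 | 0.1% | 0.2% |
| 0.4 / 0.1 / 0.5 | 0.8 | 2.0% | 2.2% |
| 0.3 / 0.3 / 0.4 | 1.3 | 11% | 12% |
| 0.2 / 0.3 / 0.5 | 1.4 | 13% | 14% |
| 0 / 0.3 / 0.7 | 1.6 | 18% | 20% |

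The approximation agrees closely and suggests that the simulated upper end is slightly high. With a shared player effect only, across all numbers of sessions tried, the simulated error was 0.2 to 1.2%. A repeated-measures ANOVA on player means stayed at 4.4 to 5.6% in every setting.

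**The case against.** A reader might infer that the rating test can never be significant. The article does not support that. The floor above 0.05 needs three conditions together: at most six instruments, one rating per expert per instrument, and an asymptotic p-value. None is fixed. Eight methods is a fair count, with a floor of 0.036. Exact p-values could reach 0.0095 at four instruments: k!/((2k)!/2^k) = 24/2520. Two items per expert would give an asymptotic floor of 0.004 at three instruments. This limits the power claim but leaves the pairing problem, because an exact test or extra items would still treat ratings from the same two people as independent.

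For the timings, the error sizes rest on assumed variance shares and an assumed data layout. If times were averaged per player before the ANOVA, the ratio would be (M + E/t)/(P + M + E/t). That never exceeds 1, so only the conservative error would remain. No single direction can therefore be claimed. The article also makes the ANOVA conditional on its assumptions, and a repeated-measures reading is not wholly excluded. Against that, no alternative is named, the same term is used for the between-group baseline comparison, and independence fails by design.

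A reader might also infer that the choice of measurements rests on these two tests alone, or that methods will be kept merely because they showed change. The Discussion combines the time and expert results with the comparison of ultrasound against flexibility tests and indentometry. The Feasibility evaluation section asks about dependability and accuracy, and has the quality of the ultrasound measurements rated after each measurement. Nor is the absence of numerical progression criteria part of this point, since a condensed article may leave them to the full protocol.

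**Conclusion.** The point holds in a limited form. As written, both analyses assume an independence that the design rules out, and they serve a primary outcome. That conclusion follows from the text and needs no assumption beyond the plain reading of the two tests.

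The sizes are conditional. The rating test cannot reach 5% for up to six instruments with one rating per expert and asymptotic p-values, and from seven it needs full or near-full agreement. The type I error of the timing test lies anywhere from about 0.2% to about 20% under the assumed variance shares with up to three sessions per player. The documents give no data to narrow this range. Collection of the data is unaffected.

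**What to change.** In the Statistical analysis section:

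1. Replace the Kruskal-Wallis sentence. Report the therapist's and the investigator's ratings side by side, item by item for each instrument, without a significance test.
2. Replace the single-factor ANOVA for time economy with a mixed model that has method as a fixed effect and participant and participant-by-method as random effects. A repeated-measures ANOVA on player means is a simpler alternative. Report mean minutes per method with 95% confidence intervals.

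Neither change needs new data, since the ratings and times are already to be collected. The cost is that suitability no longer has a p-value, and the timing analysis takes slightly more work.

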## Discussion

To the best of the author’s knowledge, this proposed pilot study will be the first investigation to assess the feasibility and the quantitative impact of IAMT for the lower back on both structural and functional levels. The primary aims will be to evaluate the measurement methods used in terms of time economy and expressiveness and to create a basis to justify the sample size of future full studies.

The comparison of the ultrasound examinations with the previously more established indentometry and flexibility tests should provide information about the qualitative and quantitative properties of the novel ultrasound techniques especially in terms of their dependability and accuracy. Those results, in combination with the time economy and evaluation of the experts, are supposed to verify whether all the used measurements are necessary for future full studies.

To classify and quantify potential therapeutic effects of IAMT, possible confounding factors of the intervention, such as increased local blood flow and resulting tissue reactions or a therapist effect will be controlled by the heat group and by the attention and care the therapist gives to the placebo group. Modern and innovative techniques of ultrasound imaging initial and specific determination of thickness, compressibility, and shear motion of the single tissue layers might make it possible to examine the structural and functional properties of myofascial tissue after IAMT. These novel results may crucially provide a greater understanding of myofascial therapy, especially in IAMT of the lower back, and the potential impact of such therapy on myofascial chains. Moreover, the results may shed light on the mechanisms behind the effects of IAMT on the myofascial tissue and on the functional properties of the human body, for example, receptor stimulation or release of adhesion and fibrosis. This would allow for a better understanding of the benefits of IAMT and its subjectively perceived effects.

In this pilot investigation, modern and objective testing methods will be applied first to healthy female soccer players to evaluate the feasibility of the planned measurement protocol and treatment timeframes in the context of IAMT and, if necessary, to adapt them. Furthermore, the information generated about the effects of IAMT should build first references for the sample size calculation of further full studies. If this study protocol proves feasible to implement, the next step will be a full study. Then, studies of male soccer players and of athletes from other sports would follow. In addition, the effects of IAMT on both athletes and non-athletes with low back pain and its potential impact on strength development in healthy athletes, present an exciting spectrum of future full studies.

## Data Availability

Data sharing is not applicable to this article as no datasets have been generated or analysed to date. As soon as data have been collected and analysed, they will be available from the investigator. Results of this randomised placebo-controlled pilot study shall be published separately, once for the short-term effects and once for the long-term effects, as main articles in an appropriate journal. Results will be made available for interested colleagues through congress presentations. Moreover, every participant will receive a summary of the final study results.

## Abbreviations

ASIS: Anterior superior iliac spine
IAMT: Instrument-assisted manual therapy
L: Lumbar vertebra
M.: Musculus
Mm.: Musculi
Th: Thoracic vertebra
